### Data collection during follow-up

Epilepsy characteristics and information on neurodevelopment, other medical history, neurological examination, concomitant medications, possible treatment emergent adverse events, and sleep EEGs will be collected 1, 3, 6, and 18 months after start of treatment. Neuropsychological assessments will be repeated only after 6 and 18 months to minimise re-test bias. After 3 months, a brief assessment of cognitive performance is performed by the clinician to detect possible ongoing regression that may warrant a change of treatment. In the corticosteroid treatment group, additional safety and tolerability assessments will include monitoring of blood pressure, glucose, and protein in urine and weight monitoring once weekly plus additionally at any hospital visits (including admissions for methylprednisolone pulses, when applicable). In case of stress, high fever or illness managements in these situations will be left to treating physician and details will be recorded in eCRF.

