We hypothesise that, in comparison to treatment with clobazam, corticosteroids are more effective in improving cognitive performance and EEG abnormalities in children with encephalopathy with ESES. Based on previous studies, the difference in percentage of responders is estimated at around 25% [19]. The use of corticosteroids may be associated with more frequent or more severe side effects than clobazam.

In a multicentre randomised controlled trial with 1:1 allocation to corticosteroids and clobazam, we aim to assess whether one of the treatments is superior to the other. The following study objectives and hypotheses are addressed in a population of recently diagnosed patients with encephalopathy with ESES:

*Primary study objective*
To compare the effects of treatment with corticosteroids or clobazam on cognition at 6 months after start of the treatment.

*Secondary study objectives*
To compare the effects of treatment with corticosteroids or clobazam on sleep-induced epileptiform activity, measured as the spike wave index (SWI), in the patients’ sleep EEG.To compare the effects of treatment with corticosteroids or clobazam on the frequency of any concomitant seizures.To compare the side effects and tolerability of corticosteroids and clobazam.To compare the effects of treatment with corticosteroids and clobazam on subjective daily functioning, as measured with a visual analogue score (VAS).To assess demographic and disease-related biomarkers, including immunological biomarkers, as potential predictors of disease activity and response to treatment with corticosteroids or clobazam.

The study is conducted as a randomised open-label parallel-group controlled trial with 1:1 treatment allocation to clobazam and corticosteroid treatment arms and is aimed at proving superiority of one treatment over the other. The trial also uses a pragmatic approach, whereby participating investigators will be allowed to apply, within predetermined limits, the dosing schedules which they consider best according to their judgement and patient response. The same flexibility will also apply to the option of using i.v. versus oral steroids, which will be left to the discretion of the treating physicians.

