### Treatment

Patients will be enrolled by their treating physician/study doctor, who has no direct insight in the allocation mechanism of the randomisation module. Treatment is allocated according to an automatic online randomisation module with block randomisation stratified for centre to the two treatment regimens (1:1 ratio). The randomisation module was programmed by a data manager. The patients and treating physicians are not blinded for treatment allocation, as this was considered not feasible with two treatment arms that differ in their prescription form (in most centres, corticosteroids are given as intravenous monthly pulses, whilst clobazam is given as a tablet to be taken daily) and because the two treatments require different monitoring. The neuropsychological assessment and EEG assessment will be performed by personnel blinded for treatment:
Clobazam will be administered orally and increased to a dose of 0.5 mg/kg/day within 2 weeks. If well tolerated, dosage may be increased up to 1.2 mg/kg/day (given once daily, in the evening). Treatment with a dosage of at least 0.5 mg/kg/day will be continued for 6 months and thereafter will be either continued or tapered according to the treating physician’s preference. Clobazam is defined by active substance for this study. It is prescribed as tablets, and brand names include Frisium, Onfi, and Tapclob as well as generic products.Corticosteroids: either intravenous methylprednisolone or oral prednisolone will be used, depending on local experience and preference.Intravenous methylprednisolone will be given as monthly pulses. A dosage of 20 mg/kg will be given over 30 min once a day for 3 consecutive days, every 4 weeks, for a total period of 6 months with the intention to stop thereafter.Oral prednisolone will be administered at an initial dosage of 2 mg/kg/day (not exceeding 60 mg/day) for 1 month, followed in the 2nd through 6th month by a dosage between 1 and 2 mg/kg/day (not exceeding 60 mg/day), according to the treating physician’s judgement. Thereafter, prednisolone will be either continued or tapered according to the treating physician’s preference.

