### Statistical analysis

The primary analyses will be performed according to the intention-to-treat principle. We will also perform (secondary) analyses in patients who have completed their assigned treatment for the period of 6 months.

Continuous outcomes will be presented with means and 95% confidence intervals. These outcomes will primarily be compared between the two treatment groups using a *t* test or Mann-Whitney *U* test depending on the distribution of the data (normal vs not normal). Categorical outcomes will be presented as proportions with 95% confidence intervals. These outcomes will primarily be compared between the two treatment groups using Fisher’s exact test. Rates of (serious) adverse events will be compared in terms of risk ratios with corresponding 95% confidence intervals. We will also identify the proportion of patients that continue on the initially allocated treatment throughout the entire study period, and analyse possible predictors for discontinuation.

Although the stratified randomisation procedure intends to create two groups with equal patient characteristics, it is known that in randomised trials of < 1000 patients, there still is a risk of bias by chance [25]. Adjusted analyses are often performed to reduce the influence of the possible differences between the two treatment arms [26]. Therefore, possible predictors of treatment outcome (i.e. known prognostic factors) will be included in a multivariate logistic/linear regression model. These prognostic factors are as follows: age at ESES recording, time interval between ESES recording and inclusion, IQ levels and cognitive sum scores at enrolment, number of drugs administered before enrolment, and aetiology (unknown, structural, metabolic, genetic, immune, infectious). We will also include cytokine and autoantibody profiles as possible predictors.

The prospective design and structured follow-up schedule should minimise the amount of missing data. However, to account for possible influence of missing data, we will perform a sensitivity analysis using multiple imputation methods [27].

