Adverse events will be reported according to Good Clinical Practice (GCP) guidelines. Adverse events are defined as any undesirable medical experience occurring to a subject during the study, whether or not considered related to the investigational drug. A serious adverse event (SAE) is any untoward medical occurrence or effect that at any dose results in death, is life-threatening, requires hospitalisation or extension thereof, results in persistent or significant disability or incapacity or otherwise jeopardises the subject, or requires intervention. SUSARs are SAEs that probably relate to the investigational drug and that are unexpected with regard to the drug used. If there is any uncertainty regarding relation between the study medication and a severe adverse event, this will be discussed within the steering committee of the trial. All adverse events are recorded and reported by the sponsor. SAEs will be reported to the ethics committee that approved the study within 15 days and followed up until they have abated or until a stable situation has been reached. SUSARs will be reported to the ethics committee and competent authority of the country where the SUSAR occurred within 15 days, and for fatal or life-threatening cases, a preliminary report will be sent within 7 days. The SUSAR will be reported to the EMA EudraVigilance database. A developmental safety update report (DSUR) will be provided annually to the ethics committees and competent authorities. An overview of adverse events per study treatment will be included in the final trial publication.

We will perform an interim analysis by the time primary outcome can be analysed in half of the required patients to evaluate whether there are unexpectedly large differences in effectiveness and unexpected side effects in both treatment groups. This analysis will form the basis to determine whether continuation of the trial is ethically justified.

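### The adverse-event risk ratio pools events found by corticosteroid-only monitoring with events found by routes common to both arms, so it is open to upward detection bias

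*Protocol article*

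**What the plan says.** Under Data collection during follow-up, the schedule common to both arms is that "possible treatment emergent adverse events, and sleep EEGs will be collected 1, 3, 6, and 18 months after start of treatment". The same section continues: "In the corticosteroid treatment group, additional safety and tolerability assessments will include monitoring of blood pressure, glucose, and protein in urine". Body weight is the fourth item, and the frequency stands at the end of that sentence: "weight monitoring once weekly plus additionally at any hospital visits". Stays for pulse treatment count among those visits ("including admissions for methylprednisolone pulses, when applicable"). The Treatment section gives intravenous pulses "once a day for 3 consecutive days, every 4 weeks, for a total period of 6 months", and says that most centres use this form. It also notes that the two treatments need different monitoring, but only as a reason for not blinding.

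Under Safety and tolerability, both arms share other routes. Adverse events are asked for at study visits, parents are told to report serious events, and general practitioners are asked to report any event. An adverse event is any undesirable medical experience, whether or not related to the drug, and all are recorded.

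The Statistical analysis section fixes the comparison: "Rates of (serious) adverse events will be compared in terms of risk ratios with corresponding 95% confidence intervals". It does not distinguish how an event came to light. The Background section states the expectation: "The use of corticosteroids may be associated with more frequent or more severe side effects than clobazam".

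**The concern.** A risk ratio compares like with like only if an event has the same chance of being recorded in each arm. Here four kinds of finding are actively looked for in one arm by a schedule that the other arm does not have. A transient rise in glucose or blood pressure, or a trace of urine protein, causes no complaint. It would be recorded on corticosteroids and could pass unseen on clobazam.

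Side effects and tolerability are a stated secondary objective and outcome, and they would weigh heavily in the choice of treatment if the cognitive results were similar. The detection effect runs in the same direction as the stated expectation of more side effects on corticosteroids. A ratio above 1 could not be split into real harm and closer looking, because nothing in the planned comparison identifies the route of detection. The primary cognitive outcomes are not affected.

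**Working it through.** **No plan figure to reproduce.** The article states no adverse-event rate, detection probability or expected risk ratio. The only trial figure used below is 65 children per arm (Sample size calculation). Everything else is an assumption, and the true risk ratio is set to 1 throughout.

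**1. Contacts in the first 6 months (26.07 weeks).** Both arms have 3 common visits (months 1, 3, 6). The corticosteroid arm adds about 26 weekly checks, although the sentence can be read so that the weekly frequency applies to weight alone. Children on intravenous pulses also have 6 to 7 courses × 3 days = 18 to 21 treatment days; those on oral prednisolone do not.

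**2. A single monitored finding.** Observed ratio = detection on corticosteroids ÷ detection on clobazam. With full detection on corticosteroids: 1.0/0.5 = 2.00, 1.0/0.7 = 1.43, 1.0/0.9 = 1.11, 1.0/1.0 = 1.00.

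**3. A silent episode of L weeks, starting at random in the 26.07 weeks.** Weekly checks find every episode of a week or longer. Checks at weeks 4.345, 13.04 and 26.07 find it only if one falls inside the episode.

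| L (weeks) | Start times found at common visits (weeks) | Probability | Observed ratio |
|---|---|---|---|
| 2 | 3 × 2 = 6 | 0.23 | about 4.3 |
| 4 | 3 × 4 = 12 | 0.46 | about 2.2 |
| 8 | 4.345 + 8 + 8 = 20.345 | 0.78 | about 1.3 |
| 12 | 13.04 + 12 = 25.04 | 0.96 | about 1.04 |

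This assumes that all four items are checked weekly on corticosteroids and would be picked up at each common visit on clobazam.

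**4. Any adverse event per child.** Let q be the risk of events outside the monitored types (equally detected in both arms), p the risk of a monitored-type event, and s the detection of the latter on clobazam relative to corticosteroids. Treating the two types as independent:

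observed ratio = [1 − (1 − q)(1 − p)] ÷ [1 − (1 − q)(1 − p·s)]

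| q | p | s | Corticosteroids | Clobazam | Ratio |
|---|---|---|---|---|---|
| 0.3 | 0.2 | 0.3 | 1 − 0.7 × 0.80 = 0.440 | 1 − 0.7 × 0.94 = 0.342 | 1.29 |
| 0.5 | 0.2 | 0.5 | 1 − 0.5 × 0.80 = 0.600 | 1 − 0.5 × 0.90 = 0.550 | 1.09 |
| 0.7 | 0.1 | 0.8 | 1 − 0.3 × 0.90 = 0.730 | 1 − 0.3 × 0.92 = 0.724 | 1.01 |

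The range over q 0.3-0.7, p 0.1-0.2 and s 0.3-0.8 is about 1.01 to 1.29.

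**5. Effect on the confidence interval.** Exact binomial enumeration at 65 per arm, with log-scale 95% limits for the ratio: the lower limit exceeds 1 in about 3% to 19% of trials over the same grid, against about 2% when detection is equal (s = 1).

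**The case against.** The strongest reply is that the extra checks cover four named items only. They are not designed to find sedation or agitation, which the Background names as the frequent clobazam effects. Symptomatic and serious events have shared routes in both arms, and clobazam children also have two plasma-level samples within 6 months. This stands. It is why the any-event range is modest and why the bias lies mainly in the monitored findings. It does not help with silent findings: parents are asked to report serious events, and a general practitioner can report only what someone noticed.

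A reader might infer that poor detection on clobazam applies to every kind of event. With 95% against 50-80% detection of all events and a true risk of 40-60%, the ratio would be 1.19 to 1.90 and the interval would exclude 1 in 10% to 87% of trials. The arithmetic is correct, but the article describes no mechanism of that breadth. More hospital contact could raise reporting in general, but nothing in the document quantifies it.

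A reader might also infer that the biased ratio drives the interim decision on continuing. The text there concerns "unexpectedly large differences in effectiveness and unexpected side effects in both treatment groups". Weight gain and raised glucose are named in the Background as known concerns, and nothing ties the risk ratios to that decision.

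Nor does the serious-event definition clearly favour one arm. Extension of a hospital stay counts for any admission, and whole-night EEG recordings at follow-up are allowed in both arms.

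Two further replies are fair. Dropping corticosteroid-monitored findings from the comparison would hide the very harms of concern. And a parent told of a raised glucose between visits may repeat it at the next common visit. Both shape the fix.

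Finally, the full protocol or a statistical analysis plan may add event sets. The point here is the comparison that the article does state, which pools unequally ascertained events.

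**Conclusion.** The point holds in a limited form. The monitoring schedule differs by arm, and the stated risk ratio does not take account of it, so the ratio is open to upward bias, mainly for glucose, blood pressure, urine protein and weight. With no true difference, the any-event ratio would be about 1.01 to 1.29 under the assumed ranges. For silent findings lasting 2 to 8 weeks it would be about 4.3 down to 1.3, if all four items are checked weekly. With equal detection it is 1.00. The document supplies none of these probabilities, so the direction is likely but the size is not determined.

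The document does not support saying that an excess on corticosteroids would be due to ascertainment alone. The Background anticipates a possible true excess, and an observed ratio would mix the two. Nor does it support saying that clobazam children are seen only at the common visits. This is a worthwhile correction to a secondary safety comparison, not a threat to the primary result.

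**What to change.** 1. In the electronic case report form, add one field for how each event was first detected: common study visit, spontaneous report (parent or general practitioner), or corticosteroid-specific monitoring. Coding the first detection deals with findings that are repeated at a later common visit.
2. In Statistical analysis, base between-arm inference on the risk ratio for events ascertained by routes common to both arms, together with all serious adverse events and all discontinuations for adverse events.
3. Keep the all-event risk ratio beside it, so that no corticosteroid harm is removed from view.
4. Tabulate separately the events first found only through the corticosteroid-specific monitoring, labelled as not equally ascertained.
5. Do not exclude serious events that extend a pulse admission, and leave clinical monitoring as it is.

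The cost is one extra form field, a few lines of analysis text, and fewer events (so a wider interval) in the main comparative ratio.

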### Participant timeline

A schedule of enrolment, interventions, and assessments for participants is provided (Fig. 1).

**Fig. 1 Fig1:**
[figure not shown]
Schedule of enrolment, interventions, and assessments for participants

### Statistical analysis

The primary analyses will be performed according to the intention-to-treat principle. We will also perform (secondary) analyses in patients who have completed their assigned treatment for the period of 6 months.

Continuous outcomes will be presented with means and 95% confidence intervals. These outcomes will primarily be compared between the two treatment groups using a *t* test or Mann-Whitney *U* test depending on the distribution of the data (normal vs not normal). Categorical outcomes will be presented as proportions with 95% confidence intervals. These outcomes will primarily be compared between the two treatment groups using Fisher’s exact test. Rates of (serious) adverse events will be compared in terms of risk ratios with corresponding 95% confidence intervals. We will also identify the proportion of patients that continue on the initially allocated treatment throughout the entire study period, and analyse possible predictors for discontinuation.

Although the stratified randomisation procedure intends to create two groups with equal patient characteristics, it is known that in randomised trials of < 1000 patients, there still is a risk of bias by chance [25]. Adjusted analyses are often performed to reduce the influence of the possible differences between the two treatment arms [26]. Therefore, possible predictors of treatment outcome (i.e. known prognostic factors) will be included in a multivariate logistic/linear regression model. These prognostic factors are as follows: age at ESES recording, time interval between ESES recording and inclusion, IQ levels and cognitive sum scores at enrolment, number of drugs administered before enrolment, and aetiology (unknown, structural, metabolic, genetic, immune, infectious). We will also include cytokine and autoantibody profiles as possible predictors.

The prospective design and structured follow-up schedule should minimise the amount of missing data. However, to account for possible influence of missing data, we will perform a sensitivity analysis using multiple imputation methods [27].

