## Methods

### Study setting

Study preparations have been initiated in 22 centres with expertise in the treatment of rare paediatric epilepsy syndromes across 12 European countries. Details of the participating centres can be found under the “Trial status” section at the end of this manuscript.

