### Outcomes

The co-primary outcome measures at 6 months will be cognitive functioning, assessed with a full neuropsychological assessment (NPA):
Intelligence quotient (IQ), or developmental quotient (DQ), compared to baseline IQ/DQ. Improvement is defined as an increase by 10 IQ/DQ points.Cognitive sum score (as defined below). Improvement is defined as statistically significant when improved by at least 75% of the standard deviation (SD).

Secondary outcome measures at 6 and 18 months will include the following:
Changes in individual absolute test results, and IQ/DQ scores, compared to baseline.Changes in spike wave index (SWI) during non-REM sleep, compared with baseline SWI.Changes in seizure frequency assessed for all reported seizure types combined, with improvement being defined as at least 50% decrease as compared with baseline.Changes in subjective global daily functioning assessed with a visual analogue score (VAS) of − 5 to + 5 as compared with baseline.Safety and tolerability, as assessed by the occurrence of adverse events.Change in inflammatory markers post-treatment as compared to levels prior to treatment.Identification of autoantibodies as potential biomarkers of disease severity (TIQ, presence of developmental regression, arrest, or delay and SWI at baseline) and treatment efficacy.

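### The primary comparisons are unadjusted: the planned baseline-adjusted model ranks below them and centre, the randomisation stratum, is in no stated analysis, so the tests are valid but inefficient

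*Protocol article*

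**What the plan says.** All references are to the protocol article.

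- **Continuous outcomes** (Statistical analysis). They are presented as means with 95% confidence intervals and compared primarily by a t test or a Mann-Whitney U test, "depending on the distribution of the data (normal vs not normal".
- **Categorical outcomes** (Statistical analysis). "These outcomes will primarily be compared between the two treatment groups using Fisher’s exact test".
- **Adjusted model** (Statistical analysis). The section notes that trials below 1000 patients can be unbalanced by chance and so adds a logistic or linear regression. Its covariates are age at ESES recording, time from recording to inclusion, "IQ levels and cognitive sum scores at enrolment, number of drugs administered before enrolment, and aetiology". Cytokine and autoantibody profiles may also enter. Centre is not listed.
- **Randomisation** (Treatment). Allocation uses an "automatic online randomisation module with block randomisation stratified for centre".
- **Centres** (Study setting). "Study preparations have been initiated in 22 centres". The Discussion adds that several centres withdrew.
- **Co-primary outcomes** (Outcomes). The first is "Intelligence quotient (IQ), or developmental quotient (DQ), compared to baseline IQ/DQ", with improvement set at 10 points. For the cognitive sum score, "Improvement is defined as statistically significant when improved by at least 75% of the standard deviation (SD".

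**The concern.** Three features of the primary comparison sit badly together.

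1. The article argues that a trial of this size needs adjustment for prognostic factors, then gives the primary role to tests that cannot adjust. Baseline cognition is likely to be the strongest predictor of 6-month cognition, and it is a covariate only in the lower-ranked model.
2. Randomisation is restricted within centre, but no stated analysis reflects this. If outcomes differ between centres, the unadjusted standard error includes between-centre variation that the design has largely balanced out.
3. The continuous test is settled by the observed distribution, while the estimate is always a mean with its interval. A Mann-Whitney test does not test a difference in means, so p-value and interval can disagree.

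What is at stake is precision, in a rare disease where the Discussion reports slower recruitment than expected.

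**Working it through.** **The plan's own figures.** Inputs from Sample size calculation: 50% vs 25%, power 80%, two-sided alpha 5%, 10% dropout. With a pooled-variance z test:

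n per arm = [1.960·√(2·0.375·0.625) + 0.842·√(0.5·0.5 + 0.25·0.75)]² / 0.25² = (1.342 + 0.557)² / 0.0625 ≈ 57.7, so 58 per arm and 116 in total.

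116/0.9 = 128.9, so 129, against 130 stated. The detectable standardised difference from a two-sample t test is 0.525 at 58 per arm and 0.495 at 65 per arm, which agrees with the stated value of around 0.5. Both figures reproduce, and neither allows for covariates.

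**Baseline as a covariate.** Let σ² be the variance of the score at each visit and r the correlation between baseline and 6 months. The article gives no r, so 0.5 to 0.9 is assumed. Per-patient variances:

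- 6-month score: σ²
- change score: 2σ²(1−r)
- ANCOVA: σ²(1−r²)

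So ANCOVA relative to change = (1−r²)/[2(1−r)] = (1+r)/2, and ANCOVA relative to the 6-month score = 1−r². Power below uses the normal approximation at 58 per arm, where an unadjusted test of a 0.5 SD difference has 76.8%. The SD is that of the change score in the third column and of the 6-month score in the fifth.

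| r | ANCOVA / change | Power | ANCOVA / 6-month score | Power |
|---|---|---|---|---|
| 0.5 | 0.75 | 87.5% | 0.75 | 87.5% |
| 0.7 | 0.85 | 83.2% | 0.51 | 96.5% |
| 0.8 | 0.90 | 81.0% | 0.36 | 99.4% |
| 0.9 | 0.95 | 78.9% | 0.19 | >99.9% |

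Against a change-score test the variance falls by 5% to 25%. In evaluable patients, 116/0.95 = 122 and 116/0.75 = 155, so the gain is like adding about 6 to 39.

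**Centre.** Simulation of 116 patients in 22 unequal centres, blocks of 4, centre fitted as fixed effects, difference of 0.5 SD. Centre sizes, block size and intraclass correlation (ICC) are assumptions. Simulation error is about 0.3 points for type I error and 0.7 for power.

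| ICC | Type I error, unadjusted | Type I error, adjusted | Power, unadjusted | Power, adjusted |
|---|---|---|---|---|
| 0 | 4.5% | 4.5% | 76.7% | 73.8% |
| 0.05 | 4.9% | 5.1% | 76.2% | 75.4% |
| 0.10 | 4.2% | 5.1% | 77.4% | 78.3% |
| 0.20 | 3.2% | 4.8% | 79.0% | 83.4% |

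The two approaches are about level near an ICC of 0.1. Adjustment is clearly better at 0.20, and fixed effects cost about 3 points of power at 0. With 130/22 = 5.9 patients per centre if all 22 recruited, fixed effects are an expensive form of adjustment. A random intercept or pooled small centres should cost less, but neither was simulated.

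**Success proportion.** No variance or power gain from adjustment was calculated for the binary outcome.

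**The case against.** An unadjusted primary test backed by a pre-specified adjusted analysis is a legitimate plan, and its validity is not in question. That stands: this is a point about efficiency.

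Four stronger readings are tempting, and the documents do not support them.

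- *Baseline is ignored.* It is not. IQ/DQ is judged against baseline in Outcomes, success is defined as improvement, and baseline IQ and sum score are in the planned regression. What remains is that this regression ranks below the unadjusted tests and omits centre.
- *Adjustment would remove a third or more of the variance.* That follows only if raw 6-month scores are compared. Sample size calculation does describe the continuous version simply as IQ or sum score, so this reading is possible, but Outcomes points to change from baseline for IQ/DQ.
- *Omitting centre always inflates standard errors.* It does so only if centres differ. Any error is towards too few rejections, so there is no added false-positive risk.
- *There are two competing primary p-values.* A selection rule is stated, and its operational criterion may well be in the full protocol or analysis plan. The mismatch between a rank test and reported means is real, though minor.

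It is also fair to object that the trial is sized on success proportions, for which no gain is shown here.

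**Conclusion.** The point holds as one of efficiency and coherence. The primary tests are unadjusted, the better model is subordinate, and centre is in no stated analysis. These are facts of the text.

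The size of the loss rests on assumptions. For a change score it is 5% to 25% of the variance for r from 0.9 to 0.5, and it is larger only if raw 6-month scores are compared. For centre, the unadjusted test becomes conservative from an ICC of about 0.1, with type I error down to 3.2% at 0.20; below that there is little or no gain. The change is worth making because it costs almost nothing, but results from the present tests would not be invalid.

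**What to change.** - **Continuous co-primary outcomes.** Make the primary analysis an ANCOVA of the 6-month score on treatment and baseline score, with centre as a random intercept or small centres pooled by a rule set in advance. Fix this model whatever the distribution, and report the adjusted mean difference with its 95% confidence interval.
- **Success.** Use a logistic model with treatment, baseline score and centre (small centres pooled), reported as a standardised risk difference. Alternatively, use a Mantel-Haenszel risk difference stratified by centre or pooled centres.
- **Covariates.** Keep the primary models to these terms. The longer prognostic list belongs in secondary models, and 116 evaluable patients cannot support profiles drawn from around 100 cytokines.
- **Sensitivity.** Retain the t, Mann-Whitney and Fisher tests in this role.

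The cost is a change of wording and slightly more modelling work, since baseline scores and centre are already recorded. If centre has no effect, a few degrees of freedom are lost.
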